### Secondary outcome measures

Secondary outcome measures will be health-related quality of life, work ability, pain and pain intensity, and satisfaction with care, and we will examine the between-group differences at 3, 6, and 12 months after baseline measurement. These outcomes are selected to reflect important domains associated with work, unemployment, and return to work [30–33]. The EQ-5D-5L will be used to measure the potential changes in participants’ self-reported health-related quality of life within five domains: mobility, self-care, usual activities, pain/discomfort, and anxiety/depression. The WEMWBS measures mental well-being [34], while the PROMIS-29 will be used as the outcome for related domains: anxiety, depression, fatigue, pain (intensity and interference), physical function, sleep disturbance, and social participation [35]. Work-related outcomes include numeric scale measures in confidence in return to work and work ability a return to work self-evaluation and offers of employment. For those who have returned to work, measures include usual work patterns, job satisfaction, and the WRQF, an outcome measure linking a person’s health to the ability to meet work demands [36].

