### Statistical methods

#### Statistical methods for primary and secondary outcomes {20a}

A detailed statistical analysis plan has been finalised and agreed prior to analysis by the research team. We will report all participant flow in line with the CONSORT guideline extension for reporting RCTs conducted using cohorts and routinely collected data showing withdrawal and loss to follow-up [15]. Analyses will be conducted within TSD using Stata v17 or above (Stata Corporation, College Station, TX). Participant characteristics and outcomes will be summarised as mean and standard deviation for normally distributed continuous data or with median and ranges for data with skewed distributions or counts and percentage for categorical data. The primary analysis approach will be ‘intention-to-treat’. To account for the trial design featuring clustering in the intervention arm, generalised linear (GLM) mixed effects models will be used to estimate the between-group differences for both primary and secondary continuous outcomes, adjusting for age, gender, and duration of pain, with a random intercept for case manager. For example, we will analyse the between-group differences in sustained return to work (a binary outcome) using a generalised mixed-effect model with logit link function, the above covariates, and fitting a random effect in case manager allocation.

Secondary outcomes will also be analysed using generalised mixed models, using link functions appropriate to the outcome (e.g. where outcomes are continuous, we will use a canonical link function). In all cases, we will adjust for the same covariates (i.e. age, gender, and duration of pain). The adjusted treatment effect estimates (mean difference) between the groups will be presented as point estimates within a 95% confidence interval. Our outcome measures are largely independent and no correction for multiple testing will be done. *P*-values < 0.05 will be considered statistically significant. All tests will be two-sided.

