### Methods for additional analyses (e.g. subgroup analyses) {20b}

Analyses will be conducted on an intention-to-treat basis with a complier average causal effect analysis (CACE) investigating the causal effect of the intervention on the people who received it as intended by the original group allocation [74]. Subgroup analyses may be conducted, power permitting, to examine possible interactions between baseline anxiety, depression, and severity.

We will examine two levels of adherence: minimal and full. Minimal adherence with the intervention will be defined as the participant attending 2 weeks of the 6-week placements. Full adherence will be defined as the participant attending the full 6-week placement [75].

We will secondarily model return to work using a single day of work as the outcome by way of sensitivity analysis to compare our results with what has become common practice in the literature. Our view is that only a single day of work is not very relevant, although examining this as a secondary analysis will facilitate cross-trial comparisons. We will also model the time to return to work using survival analysis approaches (for example, zero-inflated Poisson regression or a negative binomial model, as best fits our data.)

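### The reason given for making no multiplicity correction (independent outcomes) is backwards and conflicts with the overlapping instruments, and the p < 0.05 rule is not limited to the primary outcome

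*Protocol article*

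**What the plan says.** Section {20a} of the protocol article covers the primary and the secondary outcomes together. On multiplicity it says: "Our outcome measures are largely independent and no correction for multiple testing will be done". It then sets a general rule, that p-values "< 0.05 will be considered statistically significant", and adds "All tests will be two-sided". Neither sentence is restricted to a class of outcome. The section also says that adjusted effects will be given with 95% confidence intervals. The Framework section applies superiority testing to the outcomes in the plural.

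The Secondary outcome measures section says that for these outcomes "we will examine the between-group differences at 3, 6, and 12 months after baseline measurement". On the instruments it says: "The EQ-5D-5L will be used to measure the potential changes in participants’ self-reported health-related quality of life within five domains", and two of those five domains are pain/discomfort and anxiety/depression. PROMIS-29 is to cover "anxiety, depression, fatigue, pain (intensity and interference), physical function, sleep disturbance, and social participation". WEMWBS adds mental well-being, and there are several work-related scales.

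The primary outcome is fixed elsewhere as a single contrast: sustained return to work, compared at 12 months.

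**The concern.** The fault lies in what the text states. It takes a decision (no correction), gives a reason for it, and attaches a significance rule that reaches every secondary comparison at every visit.

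The reason runs the wrong way. If the tests really were independent, each would be a fresh 5% chance of error, and the chance of at least one error would be higher than under positive correlation. The premise is also hard to square with the protocol's own list, where two questionnaires ask the same people about the same domains on three occasions.

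What is at stake is the standing of secondary findings. The abstract's aim names quality of life beside return to work, and the primary is binary, planned on 44 evaluable intervention participants and a 20-point difference. As written, the plan lets any isolated secondary p-value below 0.05 be called significant with no qualification.

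**Working it through.** **1. The plan's own figure.** The article states no family-wise error rate. The figure that can be reproduced is the sample size at one unadjusted 5% test. With 10% versus 30%, 80% power, two-sided 5%, three controls per intervention participant and a continuity correction, the result is 44 + 132 = 176, as stated. Inflating gives 132/0.8 + 44 × 1.14/0.8 = 165 + 62.7 = 227.7, or 228, as stated. This calculation concerns a single endpoint at a single time, so the multiplicity question does not touch it.

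**2. Counting the secondary tests.** The article gives no count. From the Secondary outcome measures section, for measures taken on everyone:
- EQ-5D-5L, counted as one score: 1
- WEMWBS: 1
- PROMIS-29, seven domains plus pain intensity: 8
- confidence in return to work, work ability, return-to-work self-evaluation, job offers: 4

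The total is 14, and over three visits 14 × 3 = 42. Left out are three measures for those back at work, satisfaction with care, and subgroup interactions, which are conditional on power.

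**3. If the tests are independent, as the text claims.** P(at least one) = 1 − 0.95^m.
- m = 14: 1 − 0.95^14 = 0.512
- m = 42: 1 − 0.95^42 = 0.884

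The expected number of false positives is 0.05 × m, which is 0.7 and 2.1. It does not depend on correlation.

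**4. If the tests are correlated.** The article gives no correlations, so these are assumptions. Z-statistics were simulated from a multivariate normal distribution with no true effect, with an equal correlation between outcomes and 0.5 between visits. Each was tested two-sided at 5%.

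| Correlation between outcomes | 14 tests at 12 months, either direction | 42 tests, either direction | 42 tests, favouring the intervention |
|---|---|---|---|
| 0 | 51% | 85% | 60% |
| 0.3 | 44% | 78% | 45% |
| 0.5 | 35% | 67% | 36% |
| 0.7 | 25% | 52% | 27% |

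At 12 months alone, the chance of at least one result falsely favouring the intervention runs from 12% (correlation 0.7) to 30% (correlation 0). The nominal one-directional rate for a single test is 2.5%. The 85% in the top row is below the 88% of step 3 because the visits are still correlated.

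**5. A smaller count.** Using only the four domains that open the Secondary outcome measures section, one test each at 12 months, the either-direction chance is 13% to 19% (independent: 1 − 0.95^4 = 0.185, the 19% being rounded).

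**6. Direction of the rationale.** In every column the rate falls as correlation rises. Independence is therefore the least favourable of the cases shown for the chance of at least one error.

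**The case against.** A fair defence has four parts.

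- *Secondary outcomes are often left uncorrected, and a detailed SAP exists but is not shown.* This stands as far as it goes. Leaving them uncorrected is defensible where they are declared supportive, and a missing hierarchy or key secondary could sit in the SAP and is not the complaint here. It does not rescue a published reason that is wrong, or a significance rule stated without limit.
- *There is already a hierarchy.* Also true. One primary at 12 months stands above the secondaries, and the stated primary objective concerns sustained return to work. A reader might infer from the abstract's aim that quality of life is a co-primary. The documents do not support this: the abstract's methods list it as secondary, and the quality-of-life item in the objectives concerns the impact of being unemployed with pain.
- *The harm is smaller than the two-sided figures suggest.* A reader might infer from 52% to 85% that a trial of an ineffective intervention would more likely than not report a benefit. That does not follow. Those rates include errors favouring usual care. Counting only results that favour the intervention, the rate over 42 tests is 45% or less at each positive correlation examined, and it exceeds one half only near independence, which the instruments contradict.
- *The counts of 14 and 42 are a reader's.* This stands. The article never states them, which is why the four-domain figure is shown as well.

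It should also be said that independence makes false positives more frequent only in the sense of at least one occurring. The expected number is the same at any correlation.

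**Conclusion.** Wrong as written. The independence rationale does not support omitting a correction, and it conflicts with the overlap between EQ-5D-5L and PROMIS-29 and with the repeated visits. Combined with a p < 0.05 rule that is not confined to the primary, it allows chance secondary results to be presented as significant at well above the nominal rate: in either direction, 25% to 51% at 12 months and 52% to 85% over all visits.

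These figures rest on no true effect on any secondary outcome, a count of 14, equal correlations of 0.7 to 0 between outcomes, and 0.5 between visits. Even the smallest count tried (four domains, 12 months only) gives more than twice the nominal 5%. The point concerns what may be claimed from secondary results. The primary analysis, the sample size and the effect estimates themselves are sound on this score.

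**What to change.** In section {20a}, delete the claim that the outcomes are independent. State that sustained return to work at 12 months is the only comparison tested confirmatorily, at two-sided 5%. State that the secondary outcomes and the 3- and 6-month comparisons are supportive or exploratory, reported as estimates with 95% confidence intervals and without being labelled statistically significant. Carry the same wording into the SAP if it is not already there.

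If the team wants to be able to make a claim on quality of life, it could name one key secondary to be tested only if the primary succeeds. This is optional and not part of the required change.

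The cost is a few sentences, with no extra data or participants. The one real downside is that an isolated secondary p-value below 0.05 can no longer be claimed as a positive result.

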### Framework

A superiority hypothesis testing framework will be used to compare the outcomes in the intervention group to the cohort-only group.

### Interim analyses {21b}

An independent data monitoring committee (DMC) will be convened to review material in relation to these objectives. The trial statistician will prepare such interim analyses as the DMC requests in advance, and the results of these analyses will not be reported to the rest of the trial team. The DMC will then review and make a report to the trial steering committee (TSC) who will advise the trial management group to continue, stop, or they may offer other advice as required. These committee reports will be used by the trial management group to determine if the study should continue or be prematurely terminated, for example, due to extreme success or futility. The DMC and TSC are expected to meet at least twice a year to monitor for quality, futility, and cases of overwhelming success (see SPIRIT item 21a), with their first meeting being at the end of the pre-pilot phase.

### Methods for additional analyses (e.g. subgroup analyses) {20b}

Analyses will be conducted on an intention-to-treat basis with a complier average causal effect analysis (CACE) investigating the causal effect of the intervention on the people who received it as intended by the original group allocation [74]. Subgroup analyses may be conducted, power permitting, to examine possible interactions between baseline anxiety, depression, and severity.

We will examine two levels of adherence: minimal and full. Minimal adherence with the intervention will be defined as the participant attending 2 weeks of the 6-week placements. Full adherence will be defined as the participant attending the full 6-week placement [75].

We will secondarily model return to work using a single day of work as the outcome by way of sensitivity analysis to compare our results with what has become common practice in the literature. Our view is that only a single day of work is not very relevant, although examining this as a secondary analysis will facilitate cross-trial comparisons. We will also model the time to return to work using survival analysis approaches (for example, zero-inflated Poisson regression or a negative binomial model, as best fits our data.)

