### Outcomes {12}

### Primary outcome measure

#### Sustained return to work

There is no consensus in the literature about what constitutes a sustained return to work. In trials of return-to-work interventions, outcome measures have been expressed with employment success constituting as little as one day of paid work [28]. However, we consider the focus on sustained return to work more useful and relevant [29]. Thus, in this study, the primary outcome will be the proportion of participants achieving a sustained return to work, which we define as the first 4 weeks of 50 to 100% work. We will examine the differences between the cohort group and intervention group, with differences at 12 months being the primary end-point. For a sustained return to work, the primary outcome data will be collected using Norwegian Labour and Welfare Administration registry data, and self-report data at 3, 6, and 12 months from baseline measurement in the case of missing registry data.

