### Sample size {14}

The sample size calculation is based on detecting a difference of 20% between the intervention group and the remaining cohort achieving a sustained return to work (1:3 allocation ratio). Assuming a cohort return to work rate as high as 10%, with a power of 80% and a 5% significance level, we will need data on 176 participants (132 control and 44 intervention) [13]. Allowing for a 20% loss to follow-up and a crude 14% inflation in the intervention group for an estimated design effect due to clustering by the case manager (assumptions here are an ICC of 0.01, smallest cluster size of 7 and largest of 16, and so a design effect of 1.14), we will aim to recruit 228 people [59]. If a 1:3 ratio allocation provides insufficient throughput for us to regularly form small groups of people for the work preparation session due to the proportion of people not accepting the intervention being high, we may switch to target overall balanced randomisation (1:2). In this case, our overall required sample size will be reduced to 190 in total, with the above inflations (with the same assumptions the estimated design effect will be 1.11 in this case) [59].

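### The survival analysis promised for time to return to work is illustrated only with count models that, as described, do not handle right-censoring

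*Protocol article*

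**What the plan says.** The relevant sentence is in the protocol article, Methods for additional analyses {20b}. It commits to survival analysis for time to return to work, and its only illustration is "for example, zero-inflated Poisson regression or a negative binomial model, as best fits our data". No other section names a method for censored times, whether Kaplan-Meier, Cox, parametric or discrete-time. The sentence mentions no risk set, no person-time offset and no value for people who have not returned.

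Three other statements set the scale:
- Outcomes {12} fixes the horizon ("with differences at 12 months being the primary end-point") and the sustained event ("which we define as the first 4 weeks of 50 to 100% work").
- Sample size {14} gives the comparator rate ("Assuming a cohort return to work rate as high as 10" per cent) and the target effect ("detecting a difference of 20% between the intervention group and the remaining cohort achieving a sustained return to work (1:3 allocation ratio").
- Section {20b} adds a sensitivity outcome: "We will secondarily model return to work using a single day of work as the outcome".

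**The concern.** Zero-inflated Poisson and negative binomial regressions describe counts. Time to return to work is a duration, and it is unobserved for anyone not back at work when follow-up ends or when they withdraw. A survival method uses such a person as still at risk up to that point. A count model of days needs a number for each of them, and the article supplies none. If most participants are in this position, the estimate depends more on the chosen number than on when people returned. Choosing between the two models by fit does not help, because fit cannot restore information on censoring that neither model uses. What is at stake is the size, and under one coding the direction, of a supporting result that readers will set beside the primary one.

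**Working it through.** **Inputs from the article.** Control rate 10%; difference 20 points, read as 30% in the intervention group; 132 control and 44 intervention participants with data; 80% power; two-sided 5%; horizon 12 months (365 days).

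**Reproducing the planned size.** This confirms the 30% v 10% reading.
- Pooled rate at 1:3: (0.30 + 3 × 0.10)/4 = 0.15.
- Uncorrected size of the smaller group: [1.96 × √(4/3 × 0.15 × 0.85) + 0.8416 × √(0.30 × 0.70 + 0.10 × 0.90/3)]² / 0.20² = 37.2.
- With continuity correction: (37.2/4) × [1 + √(1 + 2 × 4/(37.2 × 3 × 0.20))]² = 43.7, so 44. Then 44 + 132 = 176, as stated.
- Inflation: (132 + 44 × 1.14)/0.80 = 227.7, so 228, as stated.

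**Share censored at 12 months.** 0.90 × 132 + 0.70 × 44 = 118.8 + 30.8 = 149.6 of 176, or 85%. Expected events are 13.2 + 13.2 = 26.4.

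**Effect implied by the planning rates.** Assume constant hazards. The hazard ratio is ln(0.70)/ln(0.90) = 0.3567/0.1054 = 3.39. The matching ratio of uncapped mean times is 1/3.39 = 0.30, so return is much sooner.

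**What a count model of days estimates.** These are ratios of mean days, intervention/control, under the same constant hazards. Below 1 means sooner.
- *Non-returners set to 365.* Mean = 365 × (probability of return)/(cumulative hazard). Control: 365 × 0.10/0.1054 = 346.4. Intervention: 365 × 0.30/0.3567 = 307.0. Ratio 0.89.
- *Non-returners set to 0.* Control: 346.4 − 0.90 × 365 = 17.9. Intervention: 307.0 − 0.70 × 365 = 51.5. Ratio 2.87, which read as time says slower.
- *Returners only* (roughly the count part of a zero-inflated model). 51.5/0.30 = 171.7 v 17.9/0.10 = 179, ratio 0.96.

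**Sensitivity to the return-time assumption.** Suppose returners average the same number of days, m, in both groups. Coding 0 gives 0.30m/0.10m = 3.0 for any m. Coding 365 gives (255.5 + 0.30m)/(328.5 + 0.10m), which is 0.84, 0.91 and 0.96 for m = 100, 200 and 300.

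**Simulation.** Two scenarios were run: constant hazards, and no extra intervention hazard for the first 95 days (prompted by the feasibility study's mean wait of 94.8 days). Each used 400 trials of 44 + 132, plus one sample of 200,000 for expectations.

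| Quantity | Constant hazards | 95-day delay |
|---|---|---|
| Ratio of mean days, non-returners = 365 | 0.89 | 0.91 |
| Ratio of mean days, non-returners = 0 | 2.88 | 3.50 |
| Ratio of mean days, returners only | 0.96 | 1.15 |
| Cox hazard ratio, median over trials | 3.45 | 3.30 |
| Poisson on events with person-time offset, rate ratio | 3.38 | 3.32 |

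The Cox hazard ratio exceeded 1 in over 99% of trials. With zero coding, the negative binomial coefficient pointed the wrong way in at least 99% of trials but was significant that way in only about 2%. A convergence warning was raised during the run, so the negative binomial figures are approximate.

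**The case against.** The strongest reply is that the commitment is to survival analysis, with the count models offered only as examples. A Cox or discrete-time model would comply with the text, and the article says a detailed analysis plan has been finalised; that plan could set the model and the censoring rules. This stands, and it limits the point to the examples. It does not excuse them: the only methods offered as survival analysis are not survival methods as described.

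A reader might infer that the planned analysis will reverse the sign of the effect. The documents do not support that. Reversal needs zero coding, which appears nowhere, or, in the returners-only part, an assumed placement delay. Coding at 365 keeps the direction. In a zero-inflated model, the inflation part would still show the difference in the proportion returning. Also, if everyone were followed for the full year, the 365-day ratio would be a ratio of restricted mean times. That is a legitimate quantity, but it would have to be declared as such, and it fails once people withdraw or are lost.

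Nor do all Poisson models ignore censoring. Events with a person-time offset would be valid, though the article does not describe that use.

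A reader might also infer that the trial's own placement would count as return to work. That is not established. Outcomes {12} describes the single-day convention in the literature as paid work, and nothing says placements are paid. Placements run to at most 16 h per week, which reaches half time only if a full week is 32 h or less (16/0.50); the article gives no full-time week.

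**Conclusion.** The point holds in a limited form. The label and the examples in {20b} do not match, and with about 85% of participants censored at 12 months the mismatch has consequences. Following the examples literally would give an estimate that depends on an unstated coding: about 0.9 on the ratio of mean days at 365 (0.84 to 0.96 over the returner means tried), and about 3 at zero, against an implied hazard ratio of about 3.4.

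The 85% figure assumes that the planning rates hold and that time runs to sustained return. With the single-day event fewer would be censored, but the article gives no rate for it. The hazard ratio and the ratios of mean days rest on constant hazards or the other stated assumptions about return times.

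This is an additional analysis. The primary 12-month binary comparison and its sample size are unaffected, so the change is one to make but does not threaten the trial's main conclusion.

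**What to change.** In {20b}, and in the statistical analysis plan if it carries the same wording, replace the examples with a pre-specified method for right-censored times. Kaplan-Meier curves to 12 months with a Cox or discrete-time hazard model would serve, adjusted for age, gender and duration of pain as in the primary analysis, and censored at 12 months, withdrawal or loss. Say whether time runs to sustained return or to the first day of work. Drop the choice of model by fit. Remove the count models, or restrict them to a true count such as days worked, or to events with a person-time offset.

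Two additions are optional. One is the difference in restricted mean time to 12 months, useful if the wait for a placement makes the hazards non-proportional. The other is a clause stating that the single-day outcome means paid work outside the trial placement.

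The cost is wording only. No data are needed beyond dates of return, for which the registry is the intended source.
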